#### Patient Survey

Patient-related outcomes are assessed in a longitudinal web-based patient survey. A control group is drawn by direct matching according to specific patient characteristics by the health insurance companies. Patients in the intervention group and the matched control group receive a link to a web-based survey from their respective health insurance company at 4 time points: immediately after inclusion in the intervention group (control group: after matching) and 3, 6, and 12 months after inclusion.

The questionnaire for the intervention and control group consists of several items on health care usage, satisfaction with health care (eg, waiting times and coordination of care), and health-related quality of life (see Multimedia Appendix 1). The latter is assessed using the WHOQOL BREF [24] in all indication groups complemented by indication-specific instruments on quality of life (Q-LES-Q 18 for affective disorders, psychosis and posttraumatic stress, or adjustment disorder [25]; DEMQoL for dementia [26]; MSIS for multiple sclerosis [27], PDQ-39 for Parkinson disease [28]; SA-SIP30 for stroke [29]). In addition, sociodemographic information (eg, age and gender) and data on general health status (eg, hospitalizations and comorbidities) are assessed.

#### Provider Survey

The quality of structure and processes and provider satisfaction is evaluated with a health care provider survey. All physicians, therapists, and case managers in the NPPV network are invited to participate in a survey carried out by the Central Research Institute of Ambulatory Health Care in Germany (Zi). The Zi developed a 2-part paper questionnaire (see Multimedia Appendix 2). Part A of the baseline survey contains 72 items and asks for an evaluation of structures and processes (eg, coordination and networking in NPPV and IT structures), provider satisfaction, and finally for an assessment of health care quality and workload. Part B of the baseline survey uses 10 questions to gather information about personal data such as age, gender, and details of health profession and health services. The anonymized questionnaire collects data every year to assess changes over time (4 times during the study period). In order to make comparisons, the structure of the surveys that followed the baseline survey remains the same. There were only additions that reflect current developments, for example, information on health care services during the COVID-19 pandemic.

#### Ambulatory Claims Data and Drug Prescription Data

An analysis of ambulatory claims data and drug prescription data from the Association of Statutory Health Insurance Physicians in North Rhine aims at evaluating if physicians and therapist focus on patients with high needs. As first source, the claims data contain, among others, outpatient diagnoses coded according to the German modification of the International Classification of Diseases (ICD-10-GM) from the first quarter of 2016 to the third quarter of 2020 for statutory healthinsured individuals in North Rhine. The second data source includes pharmacologic treatments information on the prescribed medication. The 2 data sources were linked together for the analysis. No data were available for residents with private health insurance.

### Sample Size Calculation

We calculated minimum sample size for the primary outcome (overall SHI expenditures per patient in 12 months) for which we expect a reduction by 10% in the intervention group as compared to the control group (assuming a coefficient of variation of 0.96). To identify this effect with a statistical power of 80% (α=.05), a minimum sample size of 1456 patients is required in the intervention group and the control group, respectively.

For analyses of secondary outcomes, an effect size of Cohen *d*=0.3 is expected for patient’s quality of life (mean difference of 5.38 points on the WHOQOL BREF scale between the intervention group and the control group with SD=17.92 [24]). The sample size required to identify this mean difference with a power of 80% (α=.05) is 175 patients per group.

### Data Analyses

#### Overview

Patient data (SHI routine data and patient survey) are analyzed for the total sample and for different subgroups based on indication groups. There are 2 main subgroups: mental diseases (affective disorders, psychosis and posttraumatic stress, or adjustment disorder) and neurological diseases (dementia, multiple sclerosis, Parkinson disease, and stroke). If sample size is sufficient, single indications groups will be analyzed separately. There will be no linkage between the SHI routine data and patient survey. For all analyses, significance level is set to 5%.

#### Analyses in SHI Routine Data

SHI routine data are used to evaluate the primary outcome and the secondary outcomes 1-5 (see Table 2). For all outcomes, NPPV participants are compared to a control group that is matched by propensity score matching [30]. Propensity scores are calculated using the data of the first pool of control patients and the participants in a multiple regression model estimating probability of participation in the NPPV program by personal (eg, age and gender) and health characteristics in the 12 months before inclusion date (eg, hospitalizations and frequency of out-patient treatments). The control group consists of matched persons of the second pool of control patients using the estimated propensity scores. To evaluate the outcomes, multiple regression models are estimated, controlling for relevant confounders. If necessary (high intraclass correlation coefficient), multilevel models are used to account for the hierarchical data structure (patients nested in outpatient health care providers that participate in NPPV).

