**Conclusions:**

The NPPV program is the first intervention to implement a stepped model of care for both mental and neurological diseases in Germany. The analysis of several data sources and a large sample size (more than 14,000 patients) enable a comprehensive evaluation of the NPPV program.

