### Study Population and Recruitment

We plan to recruit up to 14,000 patients for the intervention group in the region of North Rhine, Germany. The enrollment period begins in December 2017 and ends in June 2021. Patients eligible for participation in the NPPV program will be identified by their regular outpatient or inpatient health care providers or by their nursing home. They will be referred to a physician or therapist within the NPPV network, who does an entry examination to check eligibility. Inclusion criteria are as follows: age≥18 years, insurance in one of the participating health insurance companies (“AOK Rheinland/Hamburg,” “Continentale BKK,” and “BKK Deutsche Bank”), and 1 or more medical condition of 7 indication groups as outlined in Table 1. Participation in the NPPV program is voluntary. All patients need to give written informed consent to participate in the program and accompanied study.

**Table 1 table1:** Medical inclusion and exclusion criteria for indication groups.

Indication group	ICD-10-GM-Codes^a^	Additional criteria
Affective disorders (including anxiety and depression, excluding mania and bipolar disorder)	F30-F39, F41.2	Inclusion when more than 3 weeks unable to work OR at least 2 hospitalizations in 2 years OR minimum score in Mini-ICF Rating for mental disorders
Psychosis (including mania and bipolar disorder)	F20- F31	Inclusion of all patients
Posttraumatic stress or adjustment disorder	F43	Inclusion of all patients
Dementia	F00, F01, G30	Inclusion of all patients
Multiple sclerosis	G35	Inclusion of all patients
Parkinson disease	G20-G22	Inclusion of all patients except vascular parkinsonism (G21.4)
Stroke	I63-I64	Inclusion of all patients with dysfunctions or disabilities, for example, spasticity or cognitive impairment

^a^ICD-10-GM: International Statistical Classification of Diseases and Related Health Problems.

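### Provider clustering in the SHI cost analysis is modelled only if the ICC is high, and only for NPPV providers; ICC size alone is the wrong trigger, and control patients have providers too

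*Protocol article*

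**What the plan says.** The Data Analyses part, under Analyses in SHI Routine Data, compares NPPV participants with propensity-score-matched controls by multiple regression on the primary outcome and secondary outcomes 1 to 5. On clustering it states: "If necessary (high intraclass correlation coefficient), multilevel models are used to account for the hierarchical data structure". The structure is then specified as "patients nested in outpatient health care providers that participate in NPPV". No value is given for what counts as high.

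The section SHI Routine Data defines two control pools. The first, patients of NPPV providers, serves only to estimate the propensity score. The matched control group comes from the second, which is restricted to patients not treated by an NPPV provider. Under Study Population and Recruitment, participants enter through a physician or therapist in the NPPV network.

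Under Sample Size Calculation, "we expect a reduction by 10% in the intervention group as compared to the control group", "assuming a coefficient of variation of 0.96", and "a minimum sample size of 1456 patients is required in the intervention group and the control group, respectively". That section mentions neither an ICC nor a design effect.

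**The concern.** Three features of the stated rule do not fit the design.

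1. **Trigger.** When treatment is separated by provider, the loss of precision depends on the product of ICC and cluster size. A rule that looks only at whether the ICC is high can switch the correction off when it is needed. Setting a numerical ICC threshold in another document would not repair this.
2. **Cluster level.** The named hierarchy contains NPPV providers only. By the pool definition no matched control has such a provider, yet every control with an index diagnosis has a treating provider. As written, even the high-ICC branch leaves clustering among controls unaddressed.
3. **Sample size.** The 1456 per group assumes independent patients, while the analysis section of the same article recognises a hierarchy.

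At stake are the coverage of the interval and the type I error for the primary outcome, 12-month SHI expenditures per patient. Patient-level propensity matching does not remove correlation between patients of the same provider. Recruiting more patients from the same set of providers raises m, and so increases the error from ignoring clustering.

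**Working it through.** **Step 1: reproduce the plan's figure.** Inputs from Sample Size Calculation: 10% reduction, coefficient of variation 0.96, α=0.05, power 80%, equal groups. Sidedness is not stated; two-sided is assumed.

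n per group = 2 × (z₀.₉₇₅ + z₀.₈₀)² × CV² / δ² = 2 × (1.960 + 0.842)² × 0.96² / 0.10² ≈ 1447 with unrounded quantiles.

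This is 0.6% below the stated 1456. A one-sided test would give 1140, which does not fit. The stated figure is therefore the formula for independent patients, with a design effect of 1.

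**Step 2: design effect.** With patients nested in providers and treatment constant within provider:

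- both arms clustered: DE = 1 + (m−1) × ICC
- only the NPPV arm clustered, equal groups: DE = [1 + (m−1) × ICC + 1] / 2

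**Step 3: consequence of ignoring it.** The computed interval has 1/√DE of its correct width, and the true type I error is 2 × [1 − Φ(1.96/√DE)].

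The document gives no ICC, provider count or cluster size, so all values of m and ICC below are assumptions. The case m=70 is 14,000 patients over an assumed 200 providers.

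| m | ICC | DE, both arms | Interval width ÷ correct width | Type I error, both arms | DE, NPPV arm only | Type I error, NPPV arm only |
|---|---|---|---|---|---|---|
| 20 | 0.01 | 1.19 | 0.92 | 7.2% | 1.095 | 6.1% |
| 70 | 0.01 | 1.69 | 0.77 | 13.2% | 1.345 | 9.1% |
| 20 | 0.05 | 1.95 | 0.72 | 16.0% | 1.475 | 10.7% |

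Worked example for m=70, ICC 0.01: DE = 1 + 69 × 0.01 = 1.69; √1.69 = 1.30; 1.96/1.30 = 1.508; 2 × [1 − Φ(1.508)] = 0.132. The first two rows have the same ICC, so the difference between them comes from cluster size alone.

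**Step 4: power at the planned scale.** The largest design effect at which 80% power survives is the analysed number per group divided by 1456. With 14,000 per group this is 14,000 / 1456 ≈ 9.6; with 10,000 it is 6.9; with 5000 it is 3.4. The SHI data cover only participants who started by March 2020, and neither their number nor the number of matched controls is stated. If accrual were even over the planned 43 months (December 2017 to June 2021, an assumption), the first 28 months would give 14,000 × 28/43 ≈ 9,100 participants and a tolerable design effect of about 6.3 with equal groups.

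**The case against.** **The plan does recognise clustering.** It commits to multilevel models when the ICC is high, so a too-narrow interval is not a certain result. This stands. The error arises only if the ICC is judged not high, clustering is then ignored, and the true ICC is above zero. Whether an ICC of 0.05 would count as high is unknown, so the 16% figure may describe a branch the plan would not take. An ICC of 0.01 is much less likely to be called high.

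**The sizes rest on assumptions.** This also stands. Controls are matched individually from all non-NPPV providers and may be thinly spread, which moves the result towards the one-arm column. Covariate adjustment may also lower the residual ICC. Neither point justifies a trigger that disregards cluster size.

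**A model with clustering in one arm only is a recognised method.** True, so the stated model can be fitted. But that model suits controls without clusters, and these controls have treating providers.

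**An article leaves model details to the full plan.** The missing threshold and variance estimator are not the point. The point is the stated rule and the stated cluster level.

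**A stronger reading to avoid.** A reader might infer that, because 1456 ignores clustering, the study does not have its stated 80% power. At exactly 1456 clustered patients per group power would indeed fall, for example to 67% at m=20 and ICC 0.02. But 1456 is given as a minimum, and the plan states: "We plan to recruit up to 14,000 patients for the intervention group". The document shows no shortfall below what clustering would require, although the unstated size of the analysed set means one cannot be strictly excluded.

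**Conclusion.** The point holds as one about the validity of the interval and test for the SHI outcomes, the primary outcome in particular. ICC size alone is the wrong trigger in a design where treatment is separated by provider, and the named hierarchy does not describe the control group. If the gate leads to clustering being ignored, the nominal 5% error becomes, under the assumed inputs, about 7% (m=20, ICC 0.01; 6% if only the NPPV arm is clustered), 13% (m=70, ICC 0.01; 9%) or 16% (m=20, ICC 0.05; 11%). The 1456 per group is arithmetically sound as a minimum for independent patients and should be read as such. A lack of power is not shown: with 14,000 per group, 80% would survive a design effect of about 9.6.

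**What to change.** - In Analyses in SHI Routine Data, remove the condition on the ICC. Always use either a provider random intercept or provider-clustered robust standard errors.
- Define the cluster as the treating (index-diagnosis) provider in both arms, so that the analysis agrees with the control-pool definition. The pools are already defined by the provider's NPPV status, so the extraction already uses provider information for controls.
- In Sample Size Calculation, label 1456 per group as the requirement for independent patients. Report alongside it the numbers actually analysed and a design effect from the observed provider sizes and ICC.

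The cost is a few words and one model option, with somewhat wider intervals as the downside. Nothing here calls for more patients. The article reports the analysis as complete, so the change can be made as a re-estimation reported beside the primary result.

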#### Patient Survey Data

For the analyses of the secondary outcomes 6-8, the data of the longitudinal survey of participants and a control group are used. The control group is drawn by direct matching with the following matching variables: inclusion diagnosis from a health care provider that is not participating in the NPPV program, 10 years age groups, gender, no resident in a care facility, no legal guardian, and grouped number of inhabitants of place of residence. To evaluate the outcomes, descriptive statistics and regression analyses are conducted using longitudinal multilevel modeling techniques.

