#### SHI Routine Data

The participating health insurance companies (“AOK Rheinland/Hamburg,” “Continentale BKK,” and “BKK Deutsche Bank”) provide claims data on inpatient treatment, outpatient treatment, rehabilitation, drug prescriptions, and incapacity to work as well as basic personal information (eg, age, gender, and insurance periods) for participants as well as for 2 pools of control patients. Selection criteria for the first pool of control patients are ICD code of inclusion diagnosis (see Table 2; secured diagnosis of an outpatient health care provider that participates in the NPPV program), age≥18 years at time of diagnosis, and no participation in other special treatment contracts regarding the inclusion diagnoses (this is a pool to generate propensity scores for matching). The second pool consists of patients with the same selection criteria as the first pool, except that these patients should not be treated by a health care provider that is participating in the NPPV program (this is the pool to draw the control group via propensity score matching).

Data are provided at the end of the study and will include data from 4 quarters before inclusion date until March 2021 on each participant that started participation at least in March 2020 and control patients. Inclusion dates for potential control patients are determined by date of inclusion diagnosis. The permission to use the routine data of the participating insurance companies was granted by the State Ministry of Employment, Health and Social Affairs in North Rhine Westphalia.

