### Strengths and Limitations

Our study has some strengths. We include 14,000 patients over 7 indication groups and analyze several different data sources (both primary and routine data). We also consider perspectives of patients, providers, and SHI in our analysis. Taken together, this enables a comprehensive evaluation of the NPPV program for patients with a wide range of mental and neurological diseases. However, our study also has some limitations. First, although we use matched control groups for the patient survey and analysis of routine data, our evaluation has a nonrandomized design. Second, we cannot completely rule out differences in disease severity between intervention and control groups. While an acutely higher disease severity increases the likelihood of being included in the program, this characteristic is not reflected in routine data used for our matching procedure. Third, we may face a selection bias in the patient survey as patients who are younger, healthier, and more educated are more likely to be willing to participate in our study. Finally, long-term effects (>24 months) on costs and patient outcomes cannot be evaluated in our analyses.

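### Survey controls are matched on no prior care use, although the insurers who match them hold it, so the quality-of-life and satisfaction contrasts carry a case-mix difference that could be partly reduced

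*Protocol article*

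**What the plan says.** All references are to the protocol article.

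- **Who matches.** Under Patient Survey: "A control group is drawn by direct matching according to specific patient characteristics by the health insurance companies".
- **On what.** Patient Survey Data (Data Analyses) gives the list as complete, not as examples: the inclusion diagnosis made by a provider outside the programme, then "10 years age groups, gender, no resident in a care facility, no legal guardian, and grouped number of inhabitants of place of residence".
- **What the insurers hold.** Under SHI Routine Data they "provide claims data on inpatient treatment, outpatient treatment, rehabilitation, drug prescriptions, and incapacity to work", and this delivery "will include data from 4 quarters before inclusion date until March 2021".
- **What the other comparison uses.** Under Analyses in SHI Routine Data, the propensity score draws on "health characteristics in the 12 months before inclusion date (eg, hospitalizations and frequency of out-patient treatments").
- **Linkage.** Data Analyses, Overview: "There will be no linkage between the SHI routine data and patient survey".
- **Entry rule.** Table 1, affective disorders: "Inclusion when more than 3 weeks unable to work OR at least 2 hospitalizations in 2 years OR minimum score in Mini-ICF Rating". Stroke patients must have dysfunctions or disabilities.
- **Acknowledged limit.** Strengths and Limitations: "While an acutely higher disease severity increases the likelihood of being included in the program, this characteristic is not reflected in routine data".
- **Survey schedule.** Both groups are surveyed at baseline and at 3, 6 and 12 months. The questionnaire also records hospitalizations and comorbidities. The analysis is a longitudinal multilevel model.

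**The concern.** The plan treats prior care as a confounder in one comparison and leaves it out of the matching for the other. In the survey, a participant with a recent admission or a long sick leave can be paired with a control who has the same diagnosis, age band and gender and a similar place of residence, but a stable course.

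For affective disorders the entry rule itself points this way. Two of the three routes in (sick leave and hospitalizations) are events of a kind that claims record, and a survey control need meet none of the three.

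At stake are quality of life (outcome 6) and satisfaction with care (outcome 7). Both are secondary, but together they answer the second research question, and quality of life has its own sample size calculation. A case-mix difference mixes earlier illness course with programme effect, and a larger sample does not shrink it.

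**Working it through.** **1. Can claims history enter later?** The evaluators receive survey and routine data unlinked, so they cannot add claims-based history to the survey model. The insurers match on a coded diagnosis from a particular type of provider, so they already use claims at that step. For claims history, matching is the only entry point. Self-reported history is different: the questionnaire collects it in both groups.

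**2. The plan's own figure.** Inputs from Sample Size Calculation: difference 5.38, SD 17.92, power 80%, α 0.05 (two-sided and 1:1 assumed).

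n per group = 2 × (1.960 + 0.842)² × (17.92 / 5.38)² ≈ 174.2, rounded up to 175. The stated 175 is reproduced, and 5.38 / 17.92 = 0.30.

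**3. Size of a level shift.** The documents report no imbalance, so these inputs are assumptions: participants exceed controls by 15 to 30 percentage points in prior-year admission, and an admission goes with 0.3 to 0.5 SD lower quality of life.

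Shift in SD = difference in share × effect of admission; points = SD shift × 17.92; share of the planned effect = points / 5.38.

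| Difference in share | Effect (SD) | Shift (SD) | Points | Share of 5.38 |
|---|---|---|---|---|
| 0.15 | 0.3 | 0.045 | 0.8 | 15% |
| 0.15 | 0.5 | 0.075 | 1.3 | 25% |
| 0.30 | 0.3 | 0.09 | 1.6 | 30% |
| 0.30 | 0.5 | 0.15 | 2.7 | 50% |

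**4. What such a shift does at 175 per group, with no baseline adjustment.** Standard error = 17.92 × √(2 / 175) = 1.92 points. Normal approximation:

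| Shift (SD) | Points | False-positive rate if no true effect | Power if the shift works against the programme |
|---|---|---|---|
| 0 | 0 | 5% | 80% |
| 0.05 | 0.90 | 7.5% | 65% |
| 0.10 | 1.79 | 15.5% | 46.5% |
| 0.15 | 2.69 | 29% | 29% |

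**5. What the baseline wave changes.** The tables in steps 3 and 4 describe an unadjusted comparison at one time point. A stable level difference is already visible at baseline and largely drops out of a baseline-adjusted contrast, so the figures are an upper bound for that component. They do not cover regression to the mean after enrolment in a bad phase, or a different course in previously hospitalized patients. Neither can be sized from the documents.

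**6. Direction.** More severely ill participants would lower the quality-of-life level and work against the programme. Regression to the mean would raise their change scores and favour it. The net sign is unknown.

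**The case against.** The strongest reply is that the design already measures case mix better than an admission flag would. Both groups have a baseline survey, and baseline quality of life is the more direct measure. This stands for stable level differences and is why the shift is given as an upper bound. It does not stand for regression to the mean or differential course.

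Second, the authors disclose possible severity differences and say acute severity is not visible in routine data. This stands in part: claims flags would not capture acute severity, so the case-mix difference can only be partly reduced. But the limitation covers what could not be matched. Admissions and incapacity for work are in the routine data.

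Third, the care-facility and guardian criteria are coarse proxies for severity and dependence. They are, but they do not separate a recently hospitalized outpatient from a stable one.

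Fourth, balance among those invited need not survive selective response to a voluntary web survey, which the article expects. This stands, and makes the model adjustment at least as important as the matching.

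Three stronger readings are tempting. A reader might infer that the whole contrast is avoidably biased, or that up to half of any observed effect would be artefact. The documents support neither: they report no admission shares, and the percentages rest on assumed inputs and ignore the baseline wave. A reader might also infer that the survey model will be unadjusted. The article names no covariates, but a condensed article commonly leaves these to the analysis plan, so this is no finding.

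**Conclusion.** The point holds as a weakness in a stated matching rule. The survey matching leaves out prior care use although the matching insurers hold it, the entry rule for affective disorders depends partly on it, and the routine-data comparison relies on it. The resulting case-mix difference in outcomes 6 and 7 could be partly reduced, not removed.

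Its size and direction are unknown. Under the assumed inputs, an unadjusted level contrast would move by 0.045 to 0.15 SD (0.8 to 2.7 points, 15% to 50% of the planned difference). With baseline in the model, the level component would be smaller. Regression to the mean, differential course and acute severity not visible in claims would remain. That controls had fewer prior admissions and less sick leave is plausible from the entry rule, but the documents do not report it.

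**What to change.** 1. **Matching.** Have the insurers add two coarse variables to the direct matching: any hospitalization in the 12 months before inclusion or matching (yes/no), and more than 3 weeks of incapacity for work in that period (yes/no/not applicable).
2. **Model.** Base the group contrast for outcomes 6 and 7 on a longitudinal model adjusted for the baseline score and for the self-reported hospitalizations and comorbidities already collected. Use the baseline-wave values, since later hospitalizations may themselves be affected by the programme.
3. **If controls have already been drawn.** The article reports enrolment and analysis as complete, so step 1 may no longer be possible. Then apply step 2 and state the remaining imbalance in prior care as a limitation specific to outcomes 6 and 7.

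**Cost.** Step 1 needs two more fields in the insurers' query, and no linkage or data transfer. It multiplies the matching cells by up to 2 × 3 = 6, so some participants may lack an exact match. How many cannot be said, because the article gives no size for the survey control pool. Step 2 uses data already collected. No stated sample size changes.
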